### Sample identification

We will conduct a PubMed search using terms relating to mechanical ventilation, synonyms for ‘duration of mechanical ventilation’ and study design, to identify a cohort of primary and senior authors that have published a trial in this area in the past 10 years.

## Methods

Study authors will be randomised to either participate in the Delphi panel as a ‘trial investigator’ stakeholder representative or not to participate (see Fig. 2). As we are using data available in the public domain, informed consent will not be sought from those not involved in the Delphi. Participants involved in the Delphi will be asked for informed consent in accordance with other participating stakeholder groups.

**Fig. 2 Fig2:**
[figure not shown]
Flowchart of randomisation in the observational cohort study. MV, mechanical ventilation

### Analysis

The primary outcome is the number and proportion of authors who have used the COS in trials reported at 5 and 10 years after the publication of the COS. Data will be compared between groups using the chi-square test. A *P* value <0.05 will indicate a statistically significant difference.

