### Aims and research questions

The primary aim is to develop a COS for trials involving patients undergoing mechanical ventilation where an aim of the intervention is to modify time spent on mechanical ventilation. The secondary aims are to determine the most valid method of gaining consensus for a COS, and to evaluate the COS uptake 5 and 10 years after its publication.

Our research questions are:Which outcomes are ranked by stakeholders as critical for inclusion in the COS?How is the ranking process influenced by the method of stakeholder group feedback during Delphi rounds?Do Delphi panel participants rank the importance of outcomes differently depending on their knowledge of the other groups’ ranking?Does participation by investigators in the Delphi panel affect their subsequent use of the COS, compared with investigators who do not participate?

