### The Delphi questionnaire and rounds

The Delphi will be managed using a bespoke online e-management system maintained by the COMET Initiative. This system has previously been used in the Management of Otitis Media with Effusion in Cleft Palate (MOMENT) study developing a COS for trials investigating otitis media with effusion in children [14]. It has been modified for this project to accommodate data collection, randomisation process, web link to the relevant questionnaire and presentation of scoring within each round.

### Round 1

We will use the most frequently reported outcomes identified from our systematic review for the first Delphi round. Participants will be asked to score each outcome using the Grading of Recommendations Assessment, Development and Evaluations (GRADE) scale of 1–9, where 1 represents least important and 9 represents most important [15]. Participants will have the option to suggest additional outcomes for inclusion in the second round. We will list outcomes in alphabetical order to avoid potential weighting. Outcomes suggested during round 1 will be reviewed and coded by two research team members to ensure they represent new outcomes; where uncertainty exists, the advisory group will be consulted. Scores attributed to each outcome will be calculated as a percentage of the total responses for all scores. This will be summarised by stakeholder groups and all outcomes will be carried forward to round 2. A flowchart of the study is shown in Fig. 1.

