### Observational cohort study

We will conduct a prospective observational cohort study to determine if participation of trial investigators in the Delphi panel increases COS uptake in comparison with investigators who did not participate, on the basis of the use of the COS in published reports of clinical trials in the decade after the COS is published.

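### The uptake comparison has two unranked primary time points under one 0.05 threshold (about 8–9% familywise error if either counts), and its report-date window dilutes the contrast

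*Protocol article*

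**What the plan says.** The rule is in the Analysis section of the protocol article's observational cohort study (the second of its two Analysis sections). The outcome is: "The primary outcome is the number and proportion of authors who have used the COS in trials reported at 5 and 10 years" after COS publication. The method is: "Data will be compared between groups using the chi-square test". The criterion is that a P "value <0.05 will indicate a statistically significant difference". The Aims section gives the two times equal standing: "to evaluate the COS uptake 5 and 10 years after its publication".

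The arms are formed by random allocation: "Study authors will be randomised to either participate in the Delphi panel as a ‘trial investigator’ stakeholder representative or not to participate". The cohort search is intended "to identify a cohort of primary and senior authors that have published a trial in this area in the past 10 years".

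The Observational cohort study section says which reports count. Uptake is judged "on the basis of the use of the COS in published reports of clinical trials in the decade after the COS is published". Only the date of the report bounds this window. No section restricts it by when a trial was designed, registered or started, and the article does not say what qualifies as having used the COS.

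**The concern.** There are two separate issues, and they act in different ways.

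**Multiplicity.** One primary outcome is assessed twice and each result can be held against 0.05. Nothing says which one answers the question. A significant difference at either time could be reported as evidence that Delphi participation raises uptake, at more than the nominal 5% error.

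**Window.** A trial reported soon after COS publication may have had its outcomes fixed years before. Such a trial says little about whether taking part changed the author's choice of outcomes. It may still resemble the COS, because the round 1 list is drawn from outcomes already in common use: "We will use the most frequently reported outcomes identified from our systematic review for the first Delphi round". Either way it adds similar background to both arms and blurs the difference. A null result at 5 years could then be misread as showing that participation does not matter.

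**Working it through.** The uptake study states no sample size, power, effect size or overall error rate, so there is no figure to reproduce. Its only number is the 0.05 threshold.

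**Step 1: bounds on the error rate.** For two tests at 0.05 with success on either:
- any dependence: at most 0.05 + 0.05 = 0.10
- independence: 1 − 0.95² = 0.0975

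**Step 2: allowing for correlation.** I take uptake as cumulative, so users at 5 years are a subset of users at 10 years. With p5 and p10 the uptake proportions under no difference between arms, the two test statistics have correlation

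r = √[p5(1 − p10) / (p10(1 − p5))]

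and the familywise error is 1 − P(|Z1| < 1.96 and |Z2| < 1.96) for a bivariate normal with that r. The article gives no expected uptake, so the pairs below are assumptions.

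| p5 | p10 | r | Familywise error |
|---|---|---|---|
| 5% | 20% | √(0.04/0.19) = 0.46 | 9.2% |
| 10% | 30% | √(0.07/0.27) = 0.51 | 9.05% |
| 20% | 40% | √(0.12/0.32) = 0.61 | 8.7% |
| 10% | 20% | √(0.08/0.18) = 0.67 | 8.5% |
| 30% | 40% | √(0.18/0.28) = 0.80 | 7.8% |

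Simulation of the uncorrected chi-square test with 50, 100 or 200 authors per arm (assumed), over all pairs except the last, gave 8.4–9.3%.

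**Step 3: effect of a repair.** With 0.025 at each time the error is 1 − 0.975² = 0.0494 under independence, 0.0465 at r = 0.5 and 0.0430 at r = 0.7. The simulations gave 3.8–4.8%. Naming a single primary time point also restores 5%.

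**Step 4: the window.** Assume a steady flow of reports and a fixed lag of L years from design to report. The share of counted reports from trials designed before COS publication is min(L/5, 1) at 5 years and min(L/10, 1) at 10 years.

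| L (years, assumed) | 5-year share | 10-year share |
|---|---|---|
| 1 | 20% | 10% |
| 2 | 40% | 20% |
| 2.5 | 50% | 25% |
| 3 | 60% | 30% |
| 4 | 80% | 40% |
| 5 | 100% | 50% |

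These are shares of trials. The endpoint counts authors, and an author with one older trial and one later trial that uses the COS is still a user. The table therefore shows direction and does not measure how much of the endpoint is affected.

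**Step 5: what dilution can cost.** As an illustration, take 100 authors per arm and undiluted uptake of 20% versus 40%, and suppose a fraction f of that use is impossible. Then p1 = 0.2(1 − f), p2 = 0.4(1 − f), d = p2 − p1, p̄ is their mean, and

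power = Φ{[d − 1.96√(2p̄(1 − p̄)/n)] / √[p1(1 − p1)/n + p2(1 − p2)/n]}.

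- f = 0: 0.88
- f = 0.4 (12% v 24%): 0.60
- f = 0.6 (8% v 16%): 0.41
- f = 0.8 (4% v 8%): 0.22

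Under no effect of participation p1 = p2 whatever f is, so the false-positive rate is not raised.

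**The case against.** The error rate exceeds 5% only if either result counts as success, and the article states no such rule. If both had to be significant, or if 5 years were an interim description of a 10-year answer, there would be no inflation. The article's emphasis on the long term leans that way. Ranking of time points is often left to a fuller plan, and uptake is only a secondary aim of the project. This makes the 8–9% conditional. It does not remove the point: the article does print the outcome, test and threshold, and that rule leaves the choice between two results open.

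On the window, a reader might infer that the 5-year result mostly reflects trials that could not have used the COS. The documents do not support this. It needs a typical lag above about 2.5 years, which they do not give, and it counts trials where the endpoint counts authors. Nor does it show bias, because authors are randomised and older trials should fall alike on both arms.

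Excluding every trial registered before COS publication from the main count is also open to challenge. Participants see the outcome list and the feedback during the Delphi rounds, before publication. A trial planned in that interval could adopt those outcomes because of participation, and exclusion would discard a real effect. That objection stands, so the restriction belongs in a sensitivity analysis.

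A reader might also suspect that only authors who publish a trial form the denominator. The article does not say so; it speaks of authors and randomises authors.

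**Conclusion.** The point holds as two separate statements.

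1. The printed rule has two unranked primary time points, one 0.05 threshold and no multiplicity rule. If significance at either is taken as success, the familywise error is about 8–9% over the assumed uptake pairs (7.8–9.2% by formula), and never more than 10%. It stays within 5% if both must be significant, but the article does not require that.
2. A window set by report date admits trials whose outcomes were fixed before the COS existed. The contrast is diluted, more at 5 than at 10 years. The size cannot be computed from the documents; it depends on an unstated lag, on how many trials each author reports, and on what counts as use. The consequence is lost power and a risk of a misleading null at 5 years.

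The two should not be merged: only the first concerns false positives. Neither affects development of the COS itself, which is the project's primary aim.

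**What to change.** In the Analysis section of the observational cohort study:

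- Name the cumulative 10-year comparison of all randomised authors as the single primary analysis, tested at 0.05. Report the 5-year comparison as secondary, with an estimate and confidence interval, and the same denominator of all randomised authors. If both times must stay primary, test each at 0.025.
- Add a prespecified sensitivity analysis that counts a trial as uptake only if it was registered, or if unregistered started, after COS publication.

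The cost is about two sentences of text and one extra date extracted from each report already being read. The downside of the first option is that the formal answer comes only at 10 years; testing at 0.025 instead means a stricter threshold at each time. The Study status section says the Delphi has not begun, so the change can be made before any uptake data exist.

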## Discussion

This paper describes the design of a multi-method study to develop a COS for ventilation trials in critical care, explore the best Delphi feedback mechanism for achieving consensus and determine if participation increases use of the COS in the long term. To our knowledge, it is the first time that the Delphi technique incorporating these methods has been used for developing a COS in this topic area. Other important features of this study are that it will provide guidance for designing Delphi studies for developing COS in critical care and a database of key stakeholder organisations that can be used for development of other critical care COS. In addition to developing the COS, this study may also shed light on controversial aspects within critical care trials.

### Study status

The Delphi study has not yet begun. Delphi panel members are currently being recruited.

## Abbreviations

COMET: Core Outcome Measures in Effectiveness Trials
CONSORT: Consolidated Standards of Reporting Trials
COS: Core outcome set
COVenT: Core Outcomes in Ventilation Trials
CTG: Clinical trial group
GRADE: Grading of Recommendations Assessment, Development and Evaluations
ICU: Intensive care unit
InFACT: International Forum for Acute Care Trialists
MOMENT: Management of Otitis Media with Effusion in Cleft Palate
NAHP: Nurses and allied health professionals
OMERACT: Outcome Measures in Rheumatology
SPIRIT: Standard Protocol Items: Recommendations for Interventional Trials
